## Abstract

**Background:**

Enteral nutrition is commonly practiced for ischemic stroke survivors with dysphagia. In Eastern Asia, nasogastric and oro-esophageal tubes are the mainstream options. However, there is a lack of rigorous clinical evidence on the effects of these two feeding methods on swallowing-related rehabilitation outcomes and clinical relevance.

**Objectives:**

This study is clinically oriented and aims to assess the effect of nasogastric versus oro-esophageal tube feeding on the degree and speed of dysphagia improvement, and aspiration symptoms.

**Methods:**

This multicenter randomized controlled trial will include 422 ischemic stroke patients with dysphagia who require tube feeding. Stratified randomization will be performed to assign participants 1:1 to the oro-esophageal or nasogastric groups. All participants will receive 15-days routine rehabilitation care and nasogastric or oro-esophageal feeding, according to their group assignment.

**Outcomes:**

The primary outcome is the dysphagia severity assessed using the Dysphagia Outcome and Severity Scale (DOSS). The secondary outcomes include time to improvement of one level from the baseline DOSS, time to oral intake, accumulation of secretions assessed using the Murray Secretion Scale, pharyngeal residue after swallowing assessed using the Yale Pharyngeal Residual Severity Rating Scale, and airway protection assessed using the Penetration-Aspiration Scale. Aspiration symptoms will be monitored for 6 weeks.

**Discussion:**

This study aims to provide evidence-based support for the comprehensive effects of tube feeding on swallowing-related rehabilitation outcomes.

**Clinical trial registration:**

ClinicalTrials.gov, identifier NCT07386834.

## Introduction

1

Dysphagia affects 30–50% of ischemic stroke survivors (1). It significantly increases the risk of malnutrition, aspiration, and subsequent pneumonia (2). Enteral nutritional support is clinically practiced for patients requiring non-oral nutrition (2). In East Asia, public acceptance of gastrostomy is relatively low, and nasogastric tubes are the primary option (3). However, several studies have shown that nasogastric tubes may increase the risk of adverse outcomes, including reflux, pharyngeal discomfort, elevated muscle tone, and psychological problems (3–5). To address these issues, intermittent oro-esophageal tube feeding was first conceptualized in 1988 (6). This method involves oral insertion of tubes into the upper esophagus. The tube is placed before each meal and removed after feeding (3). Currently, this technique is mainly adopted in China, South Korea, and Japan.

With the progress of research, some teams have begun to focus on the effects of oro-esophageal versus nasogastric tubes on multiple rehabilitation outcomes, among which swallowing function is the most representative (7). Some scholars believe that oro-esophageal tubes can improve swallowing outcomes by stimulating the posterior pharyngeal wall, improving nutritional status, and promoting mental well-being (3, 7, 8). Our pilot study showed that oro-esophageal tubes significantly improved airway protection and oral intake limitation than nasogastric feeding (8). These conclusions are also supported by some clinical evidence (7). However, the following limitations have yet to be addressed: First, it remains unclear whether there is a difference in the speed of improving swallowing outcomes between oro-esophageal and nasogastric tubes. Obviously, significant improvement within the first few days of intervention has relatively great clinical significance. Second, it is difficult to quantify clinical significance in many studies in which outcomes were assessed using continuous scores. Third, most studies focus on general swallowing outcomes, while little is known about local functional status, such as the accumulation of secretions and pharyngeal residue after swallowing. Fourth, instrumental assessments are the gold standard for dysphagia, but have not been widely used (2). Most studies adopted screening tools or observation-based assessments (7). In addition, it is unknown whether the conclusions can be generalized to inpatients with ischemic stroke, which is the most common stroke subtype. Finally, the lack of follow-up for overt aspiration and aspiration pneumonia limits our understanding of the safety differences between oro-esophageal and nasogastric feeding.

To address these issues, this protocol plans to use Flexible Endoscopic Evaluation of Swallowing (FEES) and grade assessments to quantify swallowing function in ischemic stroke survivors (9). This study aims primarily to answer the following questions: First, is there clinical significance between the effects of oro-esophageal and nasogastric tubes on swallowing function? This includes the degree, speed, and practical differences in the outcomes. Second, are some key local swallowing functions affected? Finally, aspiration symptoms, including overt aspiration and aspiration pneumonia, will be followed for a period of time after the intervention ends to explore broader impacts.

## Methods

2

### Study design and patient and public involvement

2.1

This randomized controlled study will include ischemic stroke survivors with dysphagia who require enteral nutrition support in rehabilitation departments. Participants will be randomized 1:1 into the oro-esophageal or nasogastric groups to receive enteral feeding accordingly for 14 consecutive days. The study design is shown in Figure 1. The current protocol is designed and reported according to the CONSORT and SPIRIT 2025 statements (10, 11), while referencing the TIDieR checklist (12). The public and patients had not been directly involved in the study design.

**Figure 1 fig1:**
[figure not shown]
Trial design.

### Participants

2.2

Participants will be recruited from six rehabilitation departments across five cities in China (Suzhou, Kaifeng, Xingtai, Harbin, and Zhengzhou). The inclusion criteria are as follows: (i) Age over 18 years; (ii) First-ever stroke; (iii) Ischemic stroke based on imaging data; (iv) Enteral nutritional support is required (13); (v) Stable vital signs; (vi) Clear consciousness; and (vii) Dysphagia Outcome and Severity Scale (DOSS) level 1–2 (14); (viii) Informed consent and willingness to comply with the study procedures. The exclusion criteria are as follows: (i) Dysphagia that might be caused by other etiologies or structural abnormalities of the swallowing process; (ii) Severe hepatic, renal or hematological diseases, or malignant tumors; (iii) Contraindications to tube feeding; (iv) Pregnancy or breast feeding; and (v) Anticipated discharge or transfer to other hospitals within 2 weeks.

### Randomization and blinding

2.3

Randomization will be performed after obtaining informed consent and completion of baseline assessments, conducted separately at each trial site hospital by independent researchers using SAS version 9.4. Stratified randomization will be performed according to the DOSS levels to randomly assign participants in a 1:1 ratio to the oro-esophageal or nasogastric groups, with a block size of 4 or 6. Randomization information will be stored in the Clinical Research Methodology Key Unit and will remain inaccessible to irrelevant people.

The interventionists and participants will be unblinded, as the feeding method is identifiable. Some assessments will be scheduled during the intervention period, and these assessors will be unblinded. The assessors for day-15 assessments will be independent and blinded, as the feeding tube will be removed after the intervention period ends.

### Intervention

2.4

The intervention period will last for 14 days. All participants will receive routine rehabilitation care, as shown in Table 1. These treatments adhere to local relevant guidelines (15, 16). Swallowing rehabilitation interventions will be arranged based on the Chinese Dysphagia Rehabilitation Management and Guidelines (Appendix S2) (17). There are no intergroup differences in the rehabilitation care across the trial site hospitals.

**Table 1 tab1:** A summary of the core standardized components, structure, and implementation of the intervention.

Intervention	Description	Timepoint and frequency
Risk factor control	Interventions are implemented for stroke-related risk factors, including blood pressure, blood lipid levels, blood glucose levels, tobacco and alcohol consumption, and physical activity. These interventions encompass lifestyle modifications (e.g., smoking and alcohol cessation, dietary adjustments) and pharmacological interventions (e.g., hypoglycemic agents, antihypertensive drugs).	Routine
Stroke recurrence prevention	Stroke recurrence prevention is a systematic intervention strategy aimed at reducing the risk of recurrent cerebrovascular events in patients with a history of stroke. Beyond risk factor control, pharmacological therapy is administered based on the etiological subtypes of stroke, such as aspirin, statins, and anticoagulants.	Routine
Health education	Health education is a critical component of stroke recurrence prevention that bridges the gap between clinical interventions and patient adherence, ensuring that patients and their caregivers fully understand and implement secondary prevention measures. It includes (1) Disease Knowledge Education, (2) Medication and Rehabilitation Compliance Education, (3) Lifestyle Intervention Guidance, (4) and (5) Psychological Adjustment Guidance	Day 1
Swallowing rehabilitation	All patients receive identical daily swallowing behavior rehabilitation (30–40 min/session, 6 days/week), including oral motor training, pharyngeal facilitation, swallowing maneuvers, and secretion management.	Monday to Saturday morning
Oral hygiene	Mouthwash and dental cleaning tools are used to help patients clean their oral cavity.	Every morning
Psychological intervention	Communication is conducted with patients and their caregivers to identify potential psychological issues. For those with suspected psychological problems, emotional stabilization is achieved through verbal comfort, peer-to-peer communication among patients, and meditation.	Routine
Other rehabilitation	For participants with functional impairments other than dysphagia, corresponding physical therapy and occupational therapy are arranged. As for swallowing function, distinctive interventions are provided based on the equipment available at each center, such as transcutaneous electrical stimulation, music therapy, and the Rood technique. For participants with cognitive impairment, routine cognitive training is provided once daily for approximately 30 min, including memory training, attention training, and executive function training conducted under the guidance of therapists.	After swallowing behavior rehabilitation
Nutritional support	To ensure full reproducibility and cross-center consistency, both feeding interventions follow fixed, protocolized implementation rules with identical nutritional targets, positioning, insertion/confirmation, feeding frequency, volume progression, and post-feeding care.	Routine

On the night before day 1, any prior enteral nutrition method will be discontinued. Starting from the first intervention day, the participants will receive enteral nutrition support based on their groups. Oro-esophageal feeding will be adopted for the oro-esophageal group. This silicone tube is 40 cm in length with an inner diameter of 5.4 mm, with some side holes at the tip and a syringe connector at the distal end, as shown in Appendix S1. During feeding, the participants will be instructed to be in a sitting or semi-sitting position. A trained nurse will slowly insert the tube into the upper esophagus via the corner of the mouth. Successful placement of the tube can be confirmed by the following conditions: (1) The nurse place the distal end of the tube under water, and no bubbles appear when the participant exhales; and (2) When the nurse gently rotates the tube, the resistance is normal and the participant does not cough. The initial feeding amount is 200 mL, which is increased by 50 mL per meal until reaching the participant’s daily dietary intake. Feeding will be performed 4–6 times daily, alternating between food and water. The feeding tube is removed after each feeding (3, 17). For the nasogastric group, successful tube placement can be confirmed by aspirating gastric juice with a syringe after the feeding tube is inserted. The nasogastric tube is secured to the user’s face, and feeding is administered in accordance with local nasogastric feeding guidelines (18). The nutritional standards are identical for both groups: daily caloric intake of 20–35 kcal/kg of body weight, with a carbohydrate-to-lipid ratio of 7:3 to 6:4. Daily protein demands are estimated using the 24-h urinary urea nitrogen (19).

### Outcomes

2.5

Several assessment timepoints are defined as follows: baseline (T0), after the intervention period ends at day 15 (T1), and follow-up at day 43 (T2). The SPIRIT participant timeline is shown in Figure 2 (10).

**Figure 2 fig2:**
[figure not shown]
SPIRIT 2025 diagram of the schedule of enrollment, interventions, and assessments.

#### Secondary outcomes

2.5.2

Based on the FEES at T0 and T1, (1) the Murray Secretion Scale (MSS), (2) the Yale Pharyngeal Residual Severity Rating Scale (YPR-SRS), and the Penetration-Aspiration Scale (PAS) will be used to assess the accumulation of secretions, pharyngeal residue after swallowing, and airway protection (26–28). The MSS, YPR-SRS, and PAS are ordinal four-, five-, and eight-level scales, respectively, with higher grades indicating more severe conditions. The MSS, YPR-SRS, and PAS are assessor-blinded. (4) The time to improvement of one level from the baseline DOSS will be recorded (14). A one-level increase in the DOSS is considered clinically significant as it indicates reduced need for non-oral feeding, lower risk of aspiration and pneumonia, earlier transition to oral intake, and improved functional independence. However, it is apparently impractical to conduct daily instrumental swallowing assessments. Therefore, a three-step decision-making strategy is designed to determine clinical improvement. First, researchers will conduct preliminary evaluations by observing the participants’ daily conditions, feeding, and swallowing training performance. Participants identified as having the potential for a one-level improvement will undergo a swallowing screen, which will be compared with the baseline results for definitive evaluations. Then, detailed communication will be conducted to obtain participants’ perception of the swallowing condition. Subsequently, researchers will decide whether to conduct an additional FEES to verify the degree of the DOSS improvement. This design is intended to minimize intra-individual heterogeneity in swallowing assessments and to incorporate patient performance, patient perceptions, caregiver observations, and instrumental assessments, with details shown in Appendix S3. (5) Time to oral intake will be recorded, defined as the first day, during the two-week intervention period, on which a participant meets level 3 or above on the Dysphagia Outcome and Severity Scale. (6) Aspiration symptoms will be monitored for 6 weeks. Participants will be instructed to record daily on a paper or electronic calendar the occurrence of overt aspiration, the materials causing the aspiration, and whether the aspiration is resolved. Overt aspiration is defined as coughing or discomfort triggered by the aspiration of food or water into the airway (29). Resolution of aspiration is defined as the disappearance of discomfort with behavioral steps, such as coughing or back patting. To address potential recall bias and underreporting of aspiration, some measures are taken, as shown in Appendix S4. To monitor silent aspiration, new-onset aspiration pneumonia will be tracked over a 6-week period (Appendix S4). After discharge, this study will accept aspiration pneumonia diagnosed by qualified physicians at any tertiary hospital, as long as the primary diagnosis is coded as ICD-10 J69.0 or the patient is explicitly diagnosed with aspiration pneumonia (30). The time to improvement of one level from the baseline DOSS, time to oral intake, and aspiration symptoms are open-label assessments.

### Adverse events

2.6

Any adverse event will be monitored throughout the intervention period. Both researchers and participants will be instructed to report any unexpected events. Based on previous studies (8), some typical potential adverse events have been predefined and communicated to researchers and participants, including reflux, vomiting, abdominal distension, throat or pharyngeal discomfort, fever, and aspiration pneumonia. All adverse events will be continuously monitored, graded, and subjected to etiological analyses. Serious adverse events will be reported to the data-monitoring committee for third-party oversight.

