### Ethical considerations and monitoring

2.10

This protocol has been approved by the Ethics Committee of the First Affiliated Hospital of Zhengzhou University (No. 2026-KY-0016), and was registered at ClinicalTrials.gov (NCT07386834, 02/04/2026). This study will adhere to the Declaration of Helsinki. Prior to randomization, all participants must provide written informed consent. Members of the Data Monitoring Committee are independent from the sponsors and funders. They will focus on the incidence, severity, and association of adverse events, and have the right to suggest the termination of the study to the ethics committee for safety reasons.

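### The adverse event window stops at day 14 while follow-up runs to day 43, so late deaths and non-aspiration serious events have no stated collection and late pneumonia has no stated safety status

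*Protocol article*

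**What the plan says.** Section 2.6 (Adverse events) sets the window: "Any adverse event will be monitored throughout the intervention period". Section 2.4 (Intervention) gives its length: "The intervention period will last for 14 days". Section 2.6 also lists the adverse events expected in advance, and aspiration pneumonia is among them. On oversight it adds: "Serious adverse events will be reported to the data-monitoring committee for third-party oversight".

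Follow-up is longer. Section 2.5 places the last timepoint, T2, at day 43. Section 2.5.2 states: "Aspiration symptoms will be monitored for 6 weeks". It adds that "new-onset aspiration pneumonia will be tracked over a 6-week period", and it accepts diagnoses made at tertiary hospitals after discharge. Section 2.8 describes a phone call in week 4 that reminds participants of their aspiration records and of the study's close-out.

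Section 2.10 describes the committee's task: "They will focus on the incidence, severity, and association of adverse events". It also lets the committee suggest termination to the ethics committee on safety grounds. The Discussion names non-inferior safety as one of the results that would support wider use of oro-esophageal feeding.

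**The concern.** The article gives one clinical event two observation periods and does not connect them. Up to day 14 an aspiration pneumonia is a predefined adverse event, to be graded, examined for cause and, if serious, sent to the committee. From day 15 the same diagnosis is described only as a secondary outcome. Whether it is still graded, assessed for seriousness and reported is left open.

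Deaths and serious events of any other kind after day 14 are in a weaker position, because the article describes no means of recording them. Participants are recent stroke survivors with severe dysphagia who remain under follow-up for four more weeks.

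Two things are at stake. The first is oversight: the committee can weigh late harm only if it is recorded and passed on. The second is the safety comparison: a claim of comparable safety carries less weight if serious events other than aspiration outcomes are recorded for only the first third of the observation period.

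**Working it through.** The article gives no figure of its own to reproduce here, so the check sets the stated windows side by side.

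**Inputs**
- Adverse event window: the intervention period (2.6), 14 days (2.4).
- Aspiration symptoms and aspiration pneumonia: 6 weeks (2.5.2), 6 × 7 = 42 days.
- Last timepoint: T2, day 43 (2.5).
- Planned participants: 422 (Abstract).
- Assumption: the 6 weeks start on intervention day 1. This fits T2 at day 43. A start after day 14 would end on day 14 + 42 = 56, beyond T2.

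**Length of the gap**
- Days after the adverse event window: 42 − 14 = 28 (days 15 to 42), and 28 / 42 = 66.7%.
- Counted to T2: 43 − 14 = 29 days.
- The Abstract gives 15 days of care and feeding instead of 14. With 15 days the gap would be 42 − 15 = 27 days, and 27 / 42 = 64.3%. The point does not depend on which is meant.

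**In participant-days, with no dropout**
- Within the window: 422 × 14 = 5,908.
- After it: 422 × 28 = 11,816.
- Total: 422 × 42 = 17,724.

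**What the article describes in each part**

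| Event | Days 1–14 | Days 15–42 |
|---|---|---|
| Overt aspiration | Daily calendar (2.5.2) | Daily calendar (2.5.2) |
| Aspiration pneumonia | Adverse event (2.6) and outcome (2.5.2) | Outcome (2.5.2); adverse event status not stated |
| Other serious adverse events | Monitored (2.6) | No collection stated |
| Deaths | Not named, but within any adverse event (2.6) | No collection stated |
| Non-serious events other than aspiration | Monitored (2.6) | No collection stated |

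The 28 days are therefore not empty of safety information. The gap lies in the third and fourth rows, and in the missing link in the second row between the outcome and the adverse event system.

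**The case against.** The best defence is that the window follows exposure. Assigned feeding lasts 14 days and the tube is then removed (2.3, 2.4). Several predefined events, such as reflux, vomiting, abdominal distension and pharyngeal discomfort, plausibly belong to active feeding. The delayed risk, aspiration, is followed for the full 6 weeks. This is a coherent reason to limit general adverse event capture to 14 days, and it stands. It does not extend to deaths and serious events, nor does it explain the status of a late pneumonia.

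A second defence is that this is a condensed article. Appendix S4, the schedule in Figure 2, the full protocol and any committee charter are not shown, and one of them may set a longer reporting period. That limits how far the point can go. But section 2.6 states a window rather than leaving it open, and that window does not match sections 2.5 and 2.5.2.

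A reader might also infer more than the documents support:
- **That late events bypass the committee.** The sentence on reporting serious events has no time limit, and section 2.6 also says, without an end date, that adverse events are monitored continuously. No stated collection is not the same as events being withheld.
- **That two thirds of follow-up has no adverse event collection.** Overt aspiration and aspiration pneumonia, the latter a predefined adverse event, are collected throughout.
- **That the committee sees only serious events.** Section 2.6 says that serious events are reported, not that others are kept back, and the remit in section 2.10 covers adverse events generally.
- **That a number of missed deaths can be given.** The article states no mortality rate, and how deaths enter the pneumonia curve may be settled in an analysis plan that is not shown.

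**Conclusion.** The point holds as a mismatch of stated windows. Adverse event monitoring is tied to 14 days, while follow-up runs to day 43 and a predefined adverse event is tracked for 6 weeks. For 28 of 42 days the article states no collection of deaths or of serious events other than aspiration outcomes. It also does not say that a late pneumonia is handled as an adverse event and reported to the committee.

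The 28 days measure how long the gap lasts, not how many events fall into it; the documents give no basis for that number. The conclusion rests on reading the first sentence of section 2.6 as setting the window for the whole section, and on the 6 weeks starting at day 1. Even if the duty to report serious events is read as open-ended, it needs a means of learning of them, and after day 14 the article describes one for aspiration outcomes only. The consequence is a weaker basis for oversight and for any statement on comparable safety. The efficacy analysis is not affected. It is worth correcting because the correction is cheap.

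**What to change.** In section 2.6:
- Keep general adverse event capture for the intervention period.
- Extend collection of serious adverse events and deaths from the end of that period to T2 (day 43), using the existing fourth-week call and the T2 follow-up.
- State that aspiration pneumonia recorded after day 14 that meets seriousness criteria is reported to the data monitoring committee as a serious adverse event, as well as counted as a secondary outcome.

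If the full protocol or an appendix already provides this, the article's wording should be brought into line with it.

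The cost is the change of wording, one question on vital status and hospitalisation at contacts that already exist, and some more safety reports to process. No visit is added.
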